### 5.1.5 Sample size

We hypothesize that implementing the care pathway will reduce the mean ED-LOS with 10%. In a prospective study about the quality of Acute Care, by [name] (submitted for publication), the mean length of stay at the ED in the Maxima Medical Centre is three hours and twenty minutes (95% CI 3:00-3:40, SD=1.17). Assuming a normal distribution, a two sided test, power of 80% and a significance level ( $\alpha$ ) of 0.05, a minimum of 466 patients need to be included, 233 patients in both control and intervention group. We aim to include 300 patients in each group, with a estimated timeframe of one year. Each hospital will gather their own control-group before implementation of the care-pathway. A minimum number of control-patients will be established for each participating hospital, dependent of number of annual patient-visits at the Emergency Department.

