## 1. SUMMARY

**Rationale:** Approximately, 10-20% of older adult patients present with non-specific complaints (NSCs) at the emergency department (ED). NSCs are known as poorly described symptoms, such as 'weakness' and 'fatigue', often leading to an extensive differential diagnosis. Almost half of patients presenting with NSCs suffer from a serious underlying illness. Currently, a management protocol for patients with NSCs does not exist. Patients with NSCs are often under triaged, stay longer at the ED (ED-LOS) or hospital (HOSP-LOS) and are at a higher risk for complications during hospitalisation. A special care pathway for patients with NSCs was designed to resolve some of these problems and improve the efficiency of care at the ED.

**Objective:** To implement and evaluate a care pathway for older adults presenting with non-specific complaints at the emergency department.

**Study design:** A longitudinal multi-centre cohort with a stepped-wedge cluster design.

**Study population:** Older adults  $\geq 70$  years of age presenting with NSCs at the practice of the general practitioner (GP), the elderly care physician at a nursing home or the emergency department of the hospital will be evaluated for inclusion. Data from control patients will be collected retrospectively.

**Recruitment:** Recruitment will take place during workdays between Monday – Friday from 11:00 am – 20:00 pm and comprise of a study period of 6 months, according to the study protocol. The primary health care provider (such as a GP or elderly care physician at a nursing home) will indicate whether a patient is eligible for access to the care pathway and inform the specialist at the ED. Every referring care professional will have a card, which provides information on how to refer a patient to the care pathway and to whom. Patients can also enter the care pathway after triage at the ED, if the main complaint is non-specific. If the ED specialist registers access to the care pathway and the patient gives consent, the patient will be included and baseline data collected.

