## 5.5 STATISTICAL ANALYSIS

Primary and secondary study parameters and endpoints are described in 'Study parameters/endpoints'. All statistical analyses will be performed with SPSS 24.0 for Windows (IBS, SPSS Statistics, Chicago, IL, USA). Descriptive statistics will be used for frequencies, percentages, means and standard deviations. Continuous variables will be analysed using independent t-tests, whereas the categorical data will be analysed by chi-square or Fisher's exact test. Median and interquartile ranges of non-normally distributed categorical and metric variables of the study will be

assessed using Mann-Whitey-U-test. Prevalence of the most frequent diagnosis (coded ICD-10) at discharge will be presented in percentages. HR and corresponding 95% confidence intervals will be calculated. Generalized Estimating Equations (GEEs) will be used, which adjust for observations made within the same hospitals being more alike. All tests will be performed using a significance level of  $\alpha = 0.05$ . A two-sided p-value  $< 0.05$  will be considered significant.

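### The 466 patients and 80% power in Protocol 5.1.5 come from a formula for two independent groups, not from the stepped-wedge cluster design that the protocol declares

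*Protocol*

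**What the plan says.** The Summary names the design as "A longitudinal multi-centre cohort with a stepped-wedge cluster design". Section 4 lists five hospitals and one optional hospital.

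Section 5.1.5 sizes the study on ED length of stay, one of the two primary objectives. The hypothesis is that the pathway will "reduce the mean ED-LOS with 10"%. The reference mean, from a study at one hospital, is "three hours and twenty minutes (95% CI 3:00-3:40, SD=1.17". The calculation is introduced with "Assuming a normal distribution, a two sided test, power of 80% and a significance level" of 0.05, and concludes that "a minimum of 466 patients need to be included, 233 patients in both control and intervention group". It then adds "We aim to include 300 patients in each group".

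The section gives no ICC, number of steps, period allowance or design effect.

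Section 5.5, on the analysis, says "Generalized Estimating Equations (GEEs) will be used, which adjust for observations made within the same hospitals being more alike".

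**The concern.** A power statement holds for a particular design and analysis. In a stepped wedge, the intervention share rises as calendar time passes, so the pathway effect must be separated from time trends, and that costs information. Correlation between patients of one hospital, and variation between periods within a hospital, change the cost further. The sample size contains neither element. Yet the Summary names the design, section 5.5 names the correlation, and section 4 treats the pandemic as a serious confounder of comparisons over time.

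What is at stake is the reading of a null result on ED length of stay. With a stated 80% power it would be taken as fair evidence against a 10% reduction. If the real power is well below that, the inference is not justified.

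**Working it through.** **Inputs from section 5.1.5.** Mean 3:20 = 200 min; 10% reduction = 20 min; two-sided alpha 0.05; power 80%; 233 per group (466), target 300 per group (600). The SD is printed as 1.17, which could be 1 h 17 min (77 min) or 1.17 h (70.2 min).

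**Step 1: reproduce the plan's figure.** For independent patients, n per group = 2(1.96 + 0.8416)² SD² / 20².
- SD 77 min: 232.7, so 233 per group and 466 in total. This is an exact match.
- SD 70.2 min: 193.4, so 194 per group and 388 in total. No match.

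The SD was therefore read as 1:17, and the formula has no term for hospital or time. Under it, 233 per group gives 80% power and 300 per group gives 89%.

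**Step 2: the declared design.** Assumptions, none of them in the protocol: five hospitals, one crossing per step, six periods, equal cell sizes m = N/30, fixed period effects and random hospital effects. ρ is the ICC and r the cluster autocorrelation; r below 1 adds variation between periods within a hospital. For each hospital the covariance matrix of the period means is

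V = [σ²(1−ρ)/m + σ²ρ(1−r)] I + σ²ρr J, with σ = 77 min.

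The SE of the pathway effect is the square root of the treatment entry of (Σ Z′V⁻¹Z)⁻¹. Power = Φ(20/SE − 1.96). Detectable difference at 80% power = 2.80 × SE.

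The case ρ = 0 can be checked by hand. The share of hospitals on the pathway per period is 0, 0.2, 0.4, 0.6, 0.8, 1, so 5 × Σp(1−p) = 5 × 0.80 = 4, and Var = (σ²/m)/4.
- N = 466: m = 15.53; 5929/15.53/4 = 95.4; SE 9.77; power 53%.
- N = 600: m = 20; 5929/20/4 = 74.1; SE 8.61; power 64%.

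| ICC | r | SE, N=466 | Power, N=466 | SE, N=600 | Power, N=600 | Detectable, N=600 |
|---|---|---|---|---|---|---|
| 0 | – | 9.77 | 53% | 8.61 | 64% | 24 min (12%) |
| 0.01 | 1 | 10.88 | 45% | 9.75 | 54% | 27 min (14%) |
| 0.05 | 1 | 11.77 | 40% | 10.49 | 48% | 29 min (15%) |
| 0.05 | 0.8 | 12.47 | 36% | 11.33 | 42% | 32 min (16%) |

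Even with no hospital correlation at all, adjusting for period takes 466 patients from 80% to 53%.

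**Step 3: sensitivity to the layout (ICC 0).** Three steps (2+2+1 hospitals) give 43% with 466 and 52% with 600. Two steps (3+2) give 35% and 44%. A sixth hospital with its own step gives 55% and 66%. Reading the SD as 1.17 h in the five-step layout gives 61% and 72%. None reaches 80%.

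**Step 4: before-after within hospitals, no time effect.** With m = N/10 patients per hospital and phase, Var = (2/5)[σ²(1−ρ)/m + σ²ρ(1−r)].
- r = 1, ICC 0 to 0.05: power 80-82% (N = 466) and 89-90% (N = 600).
- r = 0.8, ICC 0.05, N = 466: 0.4 × (120.9 + 59.3) = 72.1; SE 8.49; power 65%.
- r = 0.8, ICC 0.05, N = 600: 0.4 × (93.9 + 59.3) = 61.3; SE 7.83; power 72%.

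All powers use normal quantiles with no correction for having only five clusters, so they are optimistic.

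**The case against.** The strongest reply is that the protocol never sets out a wedge in operation. The term is a label in the Summary; there is no step schedule, and section 5.5 mentions no period term. Sections 5.1.5 and 5.3.1 describe each hospital comparing its own earlier controls with its own intervention patients, and section 4 gives a single planned implementation date. On that reading Step 4 applies: 80% survives at autocorrelation 1, and with 600 patients it still holds at ICC 0.01 and autocorrelation 0.8 (86%). The wedge layout without period terms also keeps 74-80% with 466 and 84-89% with 600 (ICC 0 to 0.05, autocorrelation 1).

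This part stands: no single power figure follows from the documents, and the loss comes mainly from adjusting for time. It does not rescue the statement in 5.1.5. A comparison that ignores time is not the declared design, and it leaves the confounding described in section 4 in the estimate. Model terms may be set out in an analysis plan not seen here, but such a plan cannot make 466 patients deliver 80% under period adjustment in the layouts examined.

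A reader might also infer three stronger points that the documents do not support.
- That the trial has at most an even chance of detecting a 10% reduction. At the target of 600, power is 54% at ICC 0.01 and 64% at ICC 0.
- That the SD comes from a general ED population and is too small for these patients. Section 5.1.5 says only that the source was a study on the quality of acute care at one hospital. The Summary's remark on longer stays concerns duration, not spread, and a longer mean would make 10% larger in minutes.
- That the printed SD shows a calculation error. The adjacent interval is in hours and minutes, and 1:17 reproduces 233, so this is notation.

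**Conclusion.** The point holds as a mismatch between the declared design and the sample-size calculation. That 233 per group is the independent two-sample figure is certain, because it reproduces exactly. The 80% power is therefore not a property of the declared stepped wedge.

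The size of the shortfall is conditional. Under the five-hospital, six-period, period-adjusted layout, power is about 36-53% with 466 patients and 42-64% with 600, for ICC 0 to 0.05 and autocorrelation 1 or 0.8. The direction does not depend on the ICC chosen, since ICC 0 already misses 80%. The exact figure does depend on layout, ICC and autocorrelation, none of which the protocol states.

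**What to change.** In section 5.1.5, replace the power sentence with the power, or the detectable difference, that 466 and 600 patients give under the declared stepped-wedge model with hospital and period effects. Show it over a stated range of ICC, cluster autocorrelation and step layout, and say which layout is planned. Print the SD as 1:17 (77 min).

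The cost is a short recalculation and a change of wording. No extra patients are needed; the downside is a less favourable stated power. Re-estimating the SD from the control phase is optional. An ICC estimated from five hospitals would be too imprecise to rely on, so the range should stay in the text.

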## 5.2 STUDY PROCEDURES

The primary health care provider or GP will be the first to screen older adult patients presenting with a non-specific main complaint at their practice and will evaluate whether the patient is eligible for inclusion. Patients not referred by the GP can enter the care pathway if referred by the elderly care physician at a nursing home or if triage at the ED points to a NSC. If a patient meets all inclusion criteria, the primary health care provider will notify the specialist at the ED. Every referring care professional will have a card, which provides information on how to refer a patient to the care pathway and to whom. If possible, an ED-coach will be assigned to each participant of the care pathway, who meets the urgency criteria. The patient will be seen by an experienced doctor, according to hospital policy.

A schematic overview:

[figure not shown]

The care pathway will comprise of special attention and focused care for the patient with NSC at the ED (see paragraph 4.4)

### The APOP-screening

Each triage of the participating hospital will be trained for the APOP-screening.

The APOP-screener [11] consists of 9 questions:

Patient information, filled in by the nurse

1. Age ( $\geq 70$  year)
2. Gender
3. Did the patient arrive per ambulance?

Questions for the patient

4. Did you need help from someone? (e.g. preparing meals, housekeeping)
5. Did you need help with showering or bathing?
6. Have you been admitted to the hospital in the previous 6 months?
7. Have you been diagnosed with dementia?

- Yes, screening ended

- No, ask the following questions

- Can you reproduce the current year?

- Can you reproduce months of the year in the reverse order?

These questions lead to a risk of functional decline, cognitive decline or both, according to the APOP-screener. Four scenarios are:

1. Low risk, no supplementary actions recommended

2. High risk of functional decline - the following actions are recommended among others; in case of suspected dehydration at presentation: starting early fluid administration, in case of admission: limiting the length of stay at the ED and organizing early transfer to the ward.
3. High risk of cognitive decline - the following actions are recommended among others; Making sure the patient has a comfortable bed, has adequate lightning in the room and knows how to call for help.
4. High risk of functional and cognitive decline - the following actions are recommended among others; consider the diagnosis delirium and an internist geriatric medicine or clinical geriatrician can be consulted for a comprehensive geriatric assessment after discharge from ED.

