**Intervention:** If feasible, an ED-coach (passive or active form) will be appointed to each participant of the care pathway. The NSC will be evaluated in-depth, the patient will undergo APOP-screening during triage and if indicated, a comprehensive geriatric assessment will be performed after discharge from the ED at another department. The patient will be seen by a specialist or experienced resident in training at the ED, who will order a standard set of diagnostic tests and review the results. The APOP-risk score will guide further actions in the care pathway. A verification of the medication list will be performed <24 hours and a review of the medication will follow during admission.

**Control cohort:** Recruitment of controls will occur before implementation of the care pathway and on workdays between Monday – Friday from 11:00 am – 20:00 pm. The study period is estimated at approximately 6 months, according to study protocol. Each participating hospital will inform participants regarding their policy on data collection prior to implementing the care pathway. Data for controls within hospitals with access to CTcue will be collected retrospectively. The other participating hospitals will include eligible patients prospectively for the same estimated study period. After 30 days, the research nurse will evaluate complications that occurred after the patient leaves the care pathway.

**Main study parameters/endpoints:** Main endpoints are to evaluate the length of stay at the ED (ED-LOS) and exploring patient satisfaction on 4 established domains. Secondary objectives are evaluating the length of stay at the hospital (HOSP-LOS), discharge destination, medical diagnosis (at admission versus discharge), frequency of readmissions / revisits, 30-day mortality, loss of functional

status and costs-effectiveness of the care pathway. Study parameters are age, gender, main non-specific complaint, main diagnosis at ED-arrival and discharge, way of arrival (per ambulance, public transportation, etc.), main domain of NSC (somatic, nutrition, psychosocial, functional, mobility, falls), living situation (independent, care at home), diagnostic tests, specialist seeing the patient and consulting specialists and ED-logistics (time of arrival at ED, duration of triage, triage colour).

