### **5.1.4 Control group**

For patients included in the study as controls, the same inclusion and exclusion criteria apply.

Controls will not be specifically asked for informed consent, as each participating hospital will sign a form to collect data for control patients prior to implementing the care pathway. Additionally, it is the responsibility of each participating institution to inform their patients on the policies regarding data collection in study settings.

Obtaining the retrospective control-group will be done by CTcue, if possible. CTcue is a search engine in which unstructured data from an Electronic Health Record (EHR) can be easily found by adding specific queries in to the search engine. These data will be retrieved anonymously according to our defined in- and exclusion criteria, study parameters and endpoints. Specialists at the ED will be unaware of the patients functioning as controls during this study, since data for controls will be collected retrospectively. After 30 and 90 days, the research nurse will evaluate complications that occurred after the patient leaves the care pathway.

In the participating hospitals without access to CTcue, control patients will be gathered prospectively. The ED specialist will save the patient-number of eligible patients in the care pathway (before it is implemented). The specialist in charge of the patient is allowed to use patient data for research, without consent when data is anonymised. The specialist may grant this right to a third party, in this case the research team. This exchange of data has to be approved by the involved departments, which will be the department of Internal Medicine, Geriatrics and the Emergency Department.

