### **5.3 A SUMMARY OF THE NSC CARE PATHWAY**

1. Patients will be included in the care pathway by a general practitioner, elderly care physician or triagist at the ED. Their tasks include:
  - Check of inclusion and exclusion criteria
    - o guidelines of the study will be available on a card and in a digital format
  - Including patients via healthcare system or after contacting the specialist at the ED (internist, ED-doctor or elderly care physician)
  - Digital registration of a participant in the care pathway
2. The triagist or a trained nurse will perform the APOP, using the APOP-app on a tablet or in the electronic medical records. If possible, the ED-coordinator will assign an ED-coach to a participant of the study.
3. Every hospital will have their own system coupled to the Care Domain of the primary care provider and every participant will consent for sharing information on their frailty status. Patients will be seen by a doctor and a nurse. Three key players in this care pathway are:
  - I – Nurse
  - II – Specialist at the ED (specialist or resident in training):
    - a. in case of non-trauma patients: internist, emergency physician or elderly care physician
    - b. In case of trauma-patients: surgeon, orthopedist or emergency physician
    - c. preferably/ if possible no interns or untrained residents will see the patient with NSCIII
    - d. reviewing Frailty information from sources (primary care physician, informal caregiver, own findings, APOP; see also Appendix 1)

- ED-coach (if possible)
  - a. this can either be a secretary, nurse or a doctor
  - b. there is either no ED-coach, passive ED-coach or an active ED-coach
- 4. Tasks of the ED-coach (no ED coach, passive ED-coach or active ED-coach):
  - It is possible that no ED-coach can be appointed.

If an ED-coach can be appointed however, they can either be active or passive in patient care and perform the following tasks.

If a passive ED-coach is feasible:

- Checking progress at the ED for the participant every 30 minutes

If an active ED-coach is feasible:

- Coordinating care and communicating with the doctor and nurse taking care of the participant.
- Checking completeness of data for inclusion, reviewing medical history, calling the local responsible for medication verification <24 hours after admission, evaluating care at home, assess patient satisfaction for participant of the care pathway
  - o Checking progress at the ED for the participant every 30 minutes

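### APOP-score is listed as a baseline characteristic but is collected only as a pathway step, so a comparable value is not secured for the pre-implementation controls

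*Protocol*

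**What the plan says.** **What is listed.** Protocol section 5.4.1 has one list of baseline characteristics, not divided by group. APOP-score is in it, directly followed by adherence to the actions that APOP recommends. Section 5.3.1 says the aim is to compare each hospital's controls with its own intervention patients.

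**Where APOP is done.** The Intervention paragraph of the Summary says "the patient will undergo APOP-screening during triage". The rationale in section 2 names it among the pathway's components. Section 5.2 says "Each triage of the participating hospital will be trained for the APOP-screening". Step 2 of section 5.3 says "The triagist or a trained nurse will perform the APOP, using the APOP-app on a tablet or in the electronic medical records". Part of the screener stands under the label "Questions for the patient": needing help, help with bathing, recent admission, dementia and, where there is no dementia diagnosis, two cognition questions.

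**Where controls come from.** The Summary states "Recruitment of controls will occur before implementation of the care pathway". For CTcue hospitals, section 5.1.4 says "These data will be retrieved anonymously according to our defined in- and exclusion criteria, study parameters and endpoints". For the others it says "In the participating hospitals without access to CTcue, control patients will be gathered prospectively", and the only step described at presentation is that the ED specialist keeps the patient's number.

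**What is adjusted.** Section 5.5 names t-tests, chi-square or Fisher's exact tests, Mann-Whitney tests, and GEE to allow for similarity within hospitals. It names no case-mix covariate.

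**The concern.** The evaluation is a non-randomised comparison of patients before and after implementation, so its credibility depends on showing that the two groups are alike, or adjusting where they are not. APOP-score is the only frailty instrument in the baseline list, and the protocol describes no way for a control to receive one.

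A difference in frailty is plausible because the groups are assembled differently. Pathway patients give consent (Summary), are excluded if they refuse (5.1.3), and need a legal representative's consent if incapacitated (6.3). Controls are not specifically asked for consent (5.1.4). Pathway patients may arrive through referral cards held by GPs and nursing-home physicians (5.1.1), whereas CTcue controls are found by a query on existing records. If frailer patients are over- or under-represented in one group, the difference in ED-LOS, 30-day mortality or readmission may be credited to, or held against, the pathway.

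An analysis plan can choose covariates, but it cannot use a field that was never collected. Known dementia and admission in the previous 6 months appear in section 5.4.1 only inside APOP-score, not as fields of their own.

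**Working it through.** **1. Can a control have an APOP-score under the stated procedures?** Section 5.2 says the screener has nine questions: seven numbered items plus two cognition sub-questions.

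- Age, gender and ambulance arrival are filled in by the nurse. Section 5.4.1 collects age, gender and way of arrival anyway.
- Admission in the previous 6 months and a dementia diagnosis are asked of the patient, but a chart may also hold them.
- Needing help, help with bathing, the current year and the months in reverse are answers from the patient. A record search returns them only if someone asked and wrote them down.

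So 3 of 9 items are secured in both groups, 2 could be taken from charts, and 4 depend on screening having taken place. The protocol does not say whether any hospital screened before implementation.

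**2. What remains for adjustment?** Age, gender, way of arrival, living situation, referral category and triage colour are all listed and do not need APOP. Partial adjustment is therefore possible, but section 5.5 does not specify it.

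**3. The plan's own effect size.** Planned reduction: 10% of 3 h 20 min = 0.10 × 200 = 20 min = 0.333 h. With two-sided alpha 0.05 and 80% power,

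n per group = 2 × (1.960 + 0.842)² × SD² / 0.333².

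Reading the printed SD of 1.17 as 1 h 17 min (1.283 h) gives 233 per group, 466 in total, which matches section 5.1.5. Reading it as 1.17 decimal hours gives 194 per group, which does not. I use 1.283 h below.

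**4. Illustration of what an imbalance could do.** The documents give no APOP distribution and no ED-LOS by APOP risk, so both inputs here are assumptions:

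shift in mean ED-LOS = (difference in high-risk share) × (extra stay of high-risk patients).

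For differences of 5 to 20 percentage points and extra stays of 0.5 to 1.5 h, the shift runs from 0.05 × 30 = 1.5 min to 0.20 × 90 = 18 min. That is 7.5% to 90% of the 20-minute target.

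With the intended 300 per group, the standard error of the difference is 77 × √(2/300) = 6.29 min, ignoring clustering by hospital. Without a shift, power is 88.9%.

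| Difference in share | Extra stay | Shift | False-positive chance, no true effect | Power for a true 20-min reduction if the shift opposes it |
|---|---|---|---|---|
| 10 points | 0.5 h | 3 min | 7.6% | 77.2% |
| 10 points | 1.0 h | 6 min | 15.9% | 60.5% |
| 20 points | 0.5 h | 6 min | 15.9% | 60.5% |
| 20 points | 1.0 h | 12 min | 48.0% | 24.6% |

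The table shows only that an imbalance could matter. It is not an estimate for this trial.

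**The case against.** The strongest reply is that no passage says controls lack APOP. Section 5.1.4 has CTcue retrieve the study parameters for controls, and APOP-score is one of them. Section 5.3 allows the screening to be done in the electronic record. Controls in the other hospitals are identified prospectively. The training sentence carries no date relative to the control period, so on its own it proves nothing. All of this stands. It rules out asserting that controls have no frailty value, which a reader might infer. It does not supply a procedure: a search cannot return answers that were never recorded, and saving a patient number is not screening.

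A second reply is that adjustment is possible as things are. That is correct in part. A reader might conclude that frailty cannot be checked or adjusted at all, but the listed variables overlap with it, living situation especially.

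A third is that section 5.4.1 is a mixed list, holding items such as medication changes after review and patient satisfaction, so APOP-score may already be meant as a process measure. That is possible, but the list carries the label of baseline characteristics and the text does not separate the two kinds of item.

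A fourth is that covariates are commonly left to an analysis plan, which is not shown. That is fair for the model specification. It does not cover data fields, which have to be fixed before extraction. Because CTcue data are retrieved anonymously, returning to the charts later may not be possible.

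Finally, the same eligibility criteria apply to both groups, and nothing in the documents shows that frailty differs between them.

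**Conclusion.** The point holds in a limited form. APOP-score is listed for baseline, its collection is described only within the pathway, and nothing secures it for controls. Unless a hospital screened before implementation, it cannot be used as a between-group baseline variable or covariate, which leaves only partial case-mix adjustment.

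The documents do not support calling frailty the main prognostic difference between the groups. No passage ranks prognostic factors or reports a difference. The size and direction of any bias cannot be derived from them: the range of 1.5 to 18 minutes rests wholly on assumed imbalances and assumed extra stays, and its low end is minor.

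The change is still worth making. Taken as written, section 5.5 compares non-randomised groups with different consent routes and names no case-mix covariate, and the remedy is cheap.

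**What to change.** - **Section 5.4.1:** add hospital admission in the previous 6 months and known dementia diagnosis as separate fields, extracted by the same chart route in both groups. Pathway patients' values should also come from the chart, not from their APOP answers.
- **Section 5.5:** use these two fields, with the already listed age, gender, way of arrival and living situation, for the baseline comparison and as covariates in the GEE models for ED-LOS, 30-day mortality and readmission.
- **Section 5.4.1:** label APOP-score and APOP adherence as pathway-only process measures, except where a hospital recorded APOP before implementation, and state which hospitals did.

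**Cost:** two extra chart fields per patient and a change of wording, with no change to care. The fields may be incomplete, for example for admissions to another hospital. Without the help, bathing and cognition answers they measure frailty less fully than the whole screener, so some residual confounding will remain and should be acknowledged in the report.
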